### Measures

Quantitative data collection for Aims 1 and 2 will focus on sociodemographic information, mental health, substance use, suicidal behaviors, minority stressors, psychological processes, and other related risk and protective factors. All measures are described in Table 2, and further details regarding the primary outcomes and exposures are included below.

**Table 2 Tab2:** REALM cohort study measures

Domain	Measure	Description
***Mental health***		
Depression	Patient Health Questionnaire-9 (PHQ-9) [80]	9 items on frequency of depressive symptoms (past 2 weeks)
Suicidal ideation and attempts	Electronic Columbia Suicide Severity Rating Scale (eC-SSRS) [79]	11 items on suicidal ideation and behaviors (lifetime^c^ and past 3 months)
Anxiety	General Anxiety Disorder-7 (GAD-7) [112]	7 items on frequency of anxiety symptoms (past 2 weeks)
Post-traumatic stress	Post-Traumatic Stress Disorder Checklist for DSM-5 (PCL-5) [113]	20 items on post-traumatic stress symptoms (past month)
Substance use	Alcohol, Smoking and Substance Involvement Screening Test (ASSIST-Lite) [114]	10 items on substance use and associated impairment (past 3 months)
Alcohol use	Alcohol Use Disorder Identification Test – Concise (AUDIT-C) [115]	3 items on hazardous alcohol use (past 3 months)
Cross-cutting symptoms	DSM-5 Level 1 Cross-Cutting Symptom Measure (DSM-XC) [109]	23 items that assess the presence and severity of 13 symptom domains (past 2 weeks)
Functioning	World Health Organization Disability Assessment Schedule (WHODAS 2.0) [116]	12 items on physical, emotional, and psychological functioning (past month)
Access to and use of services	Adapted from National Survey on Drug Use and Health (NSDUH) [117]	5 items on seeking mental health care (past 3 months)
***Minority stressors***		
Stigma and discrimination	LGBTQ-Related Stigma and Discrimination Scale [59]	15 items on perceived, anticipated, and enacted stigma due to sexual orientation and/or gender identity (lifetime^c^ and past 3 months)
Intersectional discrimination	Intersectional Day-to-Day Discrimination Index [89]	9 items on general experiences of discrimination (lifetime^c^ and past 3 months)
Childhood adversity	Adverse Childhood Experiences Questionnaire^c^ [90]	10 items on adverse experiences in the first 18 years of life
General stressors	Life Events List (LEL) [91]	22 items on stressful experiences in the past year^c^ (or past 3 months)
Internalized stigma	Revised Internalized Homophobia Scale (IHP-R)^a^ [118]	5 items on negative feelings about sexual orientation (past 3 months)
	Transgender Identity Survey^b^ [119]	18 items on negative feelings about gender identity (past 3 months)
***Psychological processes***		
Hopelessness	Brief Beck Hopelessness Scale (Brief H-Neg) [120]	2 items on hopes for the future
Perceived burdensomeness	Perceived Burdensomeness Scale [121]	6 items on perceived burdensomeness to others
***Other risk and protective factors***		
Pride	Transgender Identity Survey subscale;^b^ adapted for sexual minorities^a^ [119]	8 items on pride about sexual orientation and/or gender identity (past 3 months)
Social support	Multidimensional Scale of Perceived Social Support (MSPSS) [122]	12 items on perceived social support from family, friends, and significant others
Resilience	Brief Resilience Scale [123]	6 items assessing ability to recover from stress
Flourishing	Secure Flourish [124]	12 items on happiness/life satisfaction, health, meaning and purpose, character/virtue, close relationships, and financial/material stability
General religiosity	Adapted from Rosmarin et al. [125]	4 items on religious beliefs and identity
Organizational religiosity	Adapted from Brief Multidimensional Measure of Religiosity/Spirituality [126]	3 items on organized religious activities
Religious conflict	Adapted from Eden et al. [127]	4 items religious conflict due to sexual orientation and/or gender identity
Structural religious support	Adapted from Eden et al. [127]	2 items on structural support from religious community

^a^ Sexual minorities only

^b^ Gender minorities only

^c^ Measured at baseline only

Alongside included measures, study will also capture sociodemographic information including sexual orientation, gender identity, race/ethnicity, language, education, employment status, food insecurity, income, birth country, housing, incarceration history, gender congruence/presentation/medical affirmation, attraction, and sexual orientation/gender identity disclosure/concealment

#### Primary outcomes

The primary outcomes for this study are depression, suicidal ideation, and suicide attempts. Depression will be assessed using the Patient Health Questionnaire-9 (PHQ-9) [80] and suicidal ideation and attempts will be assessed using the electronic self-reported version of the C-SSRS [79]. The PHQ-9 and the CSSR-S are validated screening tools with clinical and research applications, and have previously been used with SGM populations [81–86]. Both are part of the Suicide Prevention Resource Center's Suicide Prevention Toolkit for Primary Care Practices [87]. These assessments are relatively brief, which is expected to improve response and completion rates in the study, and they can also be scaled such that they assess experiences since last assessment. Both assessments include scale scoring that is useful for determining potential severity of symptoms as a means of differentiating risks or monitoring changes over time.

#### Primary exposures

The primary exposures for this study are distal minority stressors including stigma, discrimination, and traumatic experiences. Stigma and discrimination will be assessed using the enacted stigma subscale from the LGBTQ-Related Stigma and Discrimination Scale, developed and psychometrically evaluated by our team among SGM populations domestically and internationally [34, 59, 88]. Participants report whether they have experienced (ever and within the past three months) discrimination, violence, and harassment because of their sexual orientation and/or gender identity. We will also include the Intersectional Day-to-Day Discrimination Index, which assesses general experiences (ever and within the past three months) of discrimination, microaggressions, and harassment and has been validated for use in diverse SGM populations [89]. Traumatic experiences will be assessed using the Adverse Childhood Experiences Questionnaire [90], which evaluates childhood trauma experienced prior to age 18, and the Life Events List [91], which evaluates general stressors experienced within the past year (or the past three months at follow-up). Across these measures, specific indicators will be explored and selected for use in subsequent data analysis.

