### Data collection

Study surveys will be administered online through Alchemer, a HIPAA-compliant survey software platform that stores data in a cloud-based repository which can only be accessed by staff using individual logins and passwords. In addition to a baseline survey, all participants will be asked to complete repeated online surveys administered every three months for a total of 12 months of follow-up post-enrollment (at months 3, 6, 9, and 12). A three-month gap in assessments was chosen to give sufficient time for change to occur in exposure variables without compromising participant recall or retention, or overburdening the participants. Participants will have a total of 60 days to complete each survey from the first date of availability. Participants who miss a survey will be allowed to complete future surveys and will remain in the study unless they request to discontinue participation. Non-fraudulent participants will be compensated $20 in the form of an e-gift card for each completed survey.

Given the risk of mental illness in this population, and survey questions focused on mental health and suicide, procedures have been established to promote the safety of study participants. All participants will be provided with a mental health resource list at the completion of the survey. In addition, survey responses to the Columbia Suicide Severity Rating Scale (C-SSRS) [79] that endorse suicidal ideation with suicide intent or a suicide plan in the last three months will prompt an email alert from the survey software to study clinicians, who are trained in crisis management. Initial outreach will occur within one business day of the email alert to ensure that the participant is safe. Outreach will continue until six contact attempts have been made or the participant is reached, whichever occurs first. Study clinicians will also reach out, up to three times, to emergency contacts if other methods are unsuccessful. Once contacted, study clinicians will assess the participant’s level of risk and conduct safety planning, lethal means counseling, and/or connect the participant to a crisis hotline, as deemed appropriate by the clinical staff member.

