For Aim 2, we will use Kaplan–Meier and Cox proportional regression models to describe fixed and time-varying factors/classes and their independent associations with the incidence of self-reported symptoms of moderate or severe depression, suicidal ideation, or suicide attempts during follow-up. Model findings will be reported as adjusted hazards ratios with 95% CIs. Similar to Aim 1 analyses, we will first conduct stratified incidence analyses by SGM subgroups, with subsequent analyses exploring stratification by age and racial/ethnic identities. Guided by our theoretical framework, which combines IPTS with minority stress models, we will also implement mediation models within classes using Structural Equation Mixture Modeling [95, 96]. Secondary analyses will explore recurrent or persistent (as opposed to incident) depression and suicidal ideation using a combination of approaches that can address time-varying, repeated outcomes or changing severity of outcomes [97]. We will also conduct analyses with and without controlling for prior/lifetime reports of major depression, suicidal ideation, and/or suicide attempts, and examine the effects of potential temporality/lag for time-varying exposures that may have overlapped during periods of reported symptoms.

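### The baseline Life Events List value (past year) is not on the scale of the follow-up values (past 3 months), so it should not enter the time-varying or lagged exposures of Aim 2

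*Protocol article*

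**What the plan says.** The Primary exposures section describes the Life Events List as a measure "which evaluates general stressors experienced within the past year (or the past three months at follow-up". Table 2 (Minority stressors) agrees: "22 items on stressful experiences in the past year^c^ (or past 3 months". Superscript c in that table is defined as "Measured at baseline only". The past-year form is therefore asked once, at baseline, and the 3-month form replaces it afterwards.

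The two stigma and discrimination scales are handled differently. For the Intersectional Day-to-Day Discrimination Index, Table 2 gives "9 items on general experiences of discrimination (lifetime^c^ and past 3 months", and the LGBTQ-Related Stigma and Discrimination Scale carries the same "lifetime^c^ and past 3 months" pattern. Only the lifetime part is limited to baseline, so a 3-month value exists at every wave. The remaining trauma measure, the Adverse Childhood Experiences Questionnaire, is one "which evaluates childhood trauma experienced prior to age 18" and is fixed by design.

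Follow-up surveys are "administered every three months for a total of 12 months of follow-up post-enrollment (at months 3, 6, 9, and 12" (Data collection). For Aim 2, the Data analysis section plans Cox models to "describe fixed and time-varying factors/classes and their independent associations" with incident outcomes, and also plans to examine lag for time-varying exposures. Aim 1 uses baseline data only.

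**The concern.** The Life Events List is the only trauma exposure measured more than once, and its baseline value covers a window four times as long as each later one. A person whose rate of life events never changes will tend to report more at baseline than at month 3. The difference between the two surveys then mixes real change with the change of window.

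Three uses of the data would be affected:

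- **Lagged exposure.** If exposure is taken from the previous survey so that it precedes symptoms, the exposure for the first of the four intervals is the baseline value. That is a past-year report standing beside 3-month reports.
- **Time-varying classes.** If Life Events items are among the class indicators, item probabilities estimated on past-year reports do not carry over to 3-month reports. At an unchanged event rate, people would drift towards lower-exposure classes.
- **Change from baseline.** The article plans no such analysis of this measure by name, but any that was made would be confounded with the window.

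The window is fixed when the questionnaire is fielded. A 3-month baseline value that was not asked cannot be recovered in the analysis.

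**Working it through.** The plan states no figure on this point, so there is none to reproduce. The check is how far the change of window alone moves the measure, and what that does to a hazard ratio.

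**Inputs from the article.** Recall window of 12 months at baseline and 3 months at follow-up (Primary exposures, Table 2); four follow-up surveys three months apart (Data collection).

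**Assumptions.** The article gives no Life Events List rate, so a range is shown. The rate is constant and equal across people, and quarters are independent. The 25% and 30% rows borrow the range that the Sample size section gives for additional distal stressors over follow-up, as illustration only.

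**Step 1: apparent fall at an unchanged rate.** Expected event counts fall by 12/3 = 4. For the proportion with any event, p3 = 1 − (1 − p12)^(1/4), where p12 and p3 are the 12-month and 3-month proportions. At p12 = 30%, p3 = 1 − 0.70^0.25 = 8.5%.

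| 12-month proportion | 3-month proportion | Apparent fall (ratio) | Share of past-year reporters with an event in the last 3 months (p3/p12) |
|---|---|---|---|
| 25% | 6.9% | 3.6 | 28% |
| 30% | 8.5% | 3.5 | 28% |
| 50% | 15.9% | 3.1 | 32% |
| 70% | 26.0% | 2.7 | 37% |
| 90% | 43.8% | 2.1 | 49% |

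The relation between the 3-month and 12-month proportions is concave. If some people have persistently higher rates than others, the 12-month proportion for a given 3-month proportion is lower, and the apparent fall is smaller than tabulated.

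**Step 2: first-interval hazard ratio if the past-year value is used there.** Assume that only events in the preceding 3 months act, with a true hazard ratio of 2. People without a past-year event have relative hazard 1. Those with one are a mixture, so the ratio is about 1 + (p3/p12) × (2 − 1). At p12 = 30% this is 1 + 0.284 = 1.28; at 70% it is 1 + 0.371 = 1.37.

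**Step 3: pooled over four intervals.** A discrete-time hazard model (complementary log-log link, interval terms, 400,000 simulated people, 2% baseline risk per interval, true hazard ratio 2, exposure taken from the window before each interval) gave:

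| 12-month proportion | 3-month value in every interval | Past-year value in interval 1, 3-month values afterwards |
|---|---|---|
| 25% | 2.05 | 1.69 |
| 30% | 1.99 | 1.68 |
| 70% | 2.01 | 1.86 |

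The consistent window recovers the assumed ratio up to simulation error. The mixed window gives about 1.7 to 1.9.

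**The case against.** The strongest case against is that little of the plan has to touch the problem.

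- A reader might infer that time-varying trauma exposure cannot be put on one scale at all. The article does not support that: months 3, 6, 9 and 12 all use the 3-month window, and only the baseline value is off it. Four complete follow-up windows can also be combined to approximate a 12-month measure, though only roughly, given the 60-day completion period and missed surveys.
- A reader might infer that the first interval necessarily carries the longer window. Nothing in the article assigns the past-year value to that interval. Under concurrent coding the month 3 report covers it.
- A reader might infer that the drop after baseline biases the Cox model by itself. It does not: the model compares people at the same follow-up time, and at any one survey everyone has the same window.
- The two windows have a plausible purpose. A year gives broader exposure for the baseline classes, and three months matches the survey spacing.
- The choice of indicators is left open, and the coding of intervals is detail that an article may leave to the analysis plan.

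All of this stands and narrows the point. It does not remove it. The Data analysis section plans time-varying classes and lagged exposures, and a lagged exposure for the first interval has to come from baseline. The recall window is a questionnaire choice that the article does state, and an analysis plan can work around a missing 3-month value but cannot supply it.

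**Conclusion.** The point holds in a limited form. The baseline Life Events List value is not comparable with the follow-up values, whereas the stigma and discrimination scales do have a comparable baseline value. Follow-up exposure from month 3 to month 12, the baseline analyses of Aim 1, and Aim 1 classes used as fixed exposures in Aim 2 are sound in this respect.

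The harm is conditional on the baseline value entering a time-varying or lagged series, or classes re-derived over time. The apparent 2- to 4-fold fall then rests on an assumed constant rate and independent quarters, and is nearer an upper bound because people's rates differ. The dilution from 2 to about 1.7 to 1.9 rests further on the assumption that only recent events act and on the past-year value being used for the first interval. It shows the direction and rough size and does not forecast this study's result. The change is worth making because the gap cannot be repaired later and the remedy is small.

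**What to change.** 1. At baseline, ask the 22 Life Events items over both the past year and the past 3 months, in the way that Table 2 already pairs two windows for the stigma and discrimination scales.
2. Use the past-year version for the Aim 1 classes and as a fixed exposure in Aim 2. Use only the 3-month version in time-varying or lagged exposures and in any classes re-derived over time.
3. For participants already enrolled without the 3-month baseline item, do not lag or pool the past-year value into the 3-month series. Start the time-varying series with the month 3 report.

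The cost is one extra response column on 22 baseline items. For people already enrolled, the first interval is lost for this exposure only in lagged analyses; under concurrent coding nothing is lost.

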### Data analysis

For Aim 1, we will use latent class analysis (LCA) to explore how clusters of stigma, discrimination, and traumatic experiences (i.e., distal minority stressors) may be differentially associated with mental health-related outcomes among SGM persons at baseline. LCA is a person-centered analytic approach that allows for the identification of underlying classes of participants based on their responses to observed indicator variables [92]. Using the indicators described above to capture distal minority stressors, we will perform class enumeration by testing models with an increasing number of classes. The best fitting model will be selected using fit indices such as the Akaike Information Criteria, Bayesian Information Criteria, Vuong-Lo-Mendell-Rubin Likelihood Ratio Test, and entropy, and further evaluated based on theoretical interpretability [93]. All initial analyses will be conducted separately by the five SGM subgroups (sexual minority cisgender women, sexual minority cisgender men, transgender women and transfeminine persons, transgender men and transmasculine persons, and non-binary persons). Various modeling approaches will be examined to address potential effect modification by sexual orientation or gender identity within these five subgroups, and multigroup alignment optimization will be used to assess measurement invariance. If the latent classes are similar across subgroups, we will combine and repeat the effect modification and optimization analysis for gender minority versus cisgender participants. Finally, we will use the Bolck, Croon, and Hagenaars latent class regression approach to assess associations between class membership and prevalent depression, suicidal ideation, and suicide attempts [94]. In addition, age and racial/ethnic identities will be included as covariates, with possible interactions with latent class.

For Aim 2, we will use Kaplan–Meier and Cox proportional regression models to describe fixed and time-varying factors/classes and their independent associations with the incidence of self-reported symptoms of moderate or severe depression, suicidal ideation, or suicide attempts during follow-up. Model findings will be reported as adjusted hazards ratios with 95% CIs. Similar to Aim 1 analyses, we will first conduct stratified incidence analyses by SGM subgroups, with subsequent analyses exploring stratification by age and racial/ethnic identities. Guided by our theoretical framework, which combines IPTS with minority stress models, we will also implement mediation models within classes using Structural Equation Mixture Modeling [95, 96]. Secondary analyses will explore recurrent or persistent (as opposed to incident) depression and suicidal ideation using a combination of approaches that can address time-varying, repeated outcomes or changing severity of outcomes [97]. We will also conduct analyses with and without controlling for prior/lifetime reports of major depression, suicidal ideation, and/or suicide attempts, and examine the effects of potential temporality/lag for time-varying exposures that may have overlapped during periods of reported symptoms.

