Lastly, few studies have adopted an intersectional approach to understanding mental health disparities among SGM persons. The existing literature in this area has predominantly focused on white, cisgender samples, overlooking the unique stressors faced by individuals who experience multiple forces of marginalization [52]. Emerging research, however, has emphasized the ways in which intersecting forces of oppression and marginalization may shape mental health disparities among diverse SGM subpopulations in the US [53–55]. For instance, one longitudinal study conducted among cisgender Black, Latino, and multiracial sexual minority men found that the interaction between racial discrimination and internalized sexual orientation-related stigma contributed to greater levels of depression, anxiety, and alcohol use over the 12-month follow-up period [54]. There is also evidence that minority stress reflected in the experiences of individuals who vary in gender identity, gender expression, and sexual orientation may contribute to further mental health disparities among SGM subgroups. Indeed, several studies have suggested that individuals who identify as both sexual *and* gender minorities (e.g., gay transmasculine persons, bisexual gender non-conforming persons) have significantly worse mental health outcomes compared to those who identify only as sexual *or* gender minorities [56, 57].

In summary, there is a need for longitudinal investigations that characterize the complex and nuanced interrelationships between minority stressors, mental health conditions, and suicidal behaviors over time among heterogeneous rural SGM adults. This is necessary to create more targeted, acceptable, and impactful intervention content and strategies that mitigate stigma, promote mental health, and prevent suicidal behaviors. In response to these needs, the current study will enroll and follow a large and diverse group of SGM adults living in rural and small metropolitan areas in the US. The study has two specific aims: (1) determine whether classes of stigma, discrimination, and traumatic experiences vary across subgroups of rural SGM adults and whether these exposure classes are associated with an increased *prevalence* of depression, suicidal ideation, and suicide attempts; and (2) determine whether the classes identified in Aim 1 are associated with an increased *incidence* of depression, suicidal ideation, and suicide attempts among rural SGM adults.

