### Sample size

We based our sample size calculations on limited previous studies capturing the prevalence of depression, suicidal ideation, and suicide attempts [1, 4, 7, 33, 63–71] – as well as distal minority stressors [34, 72, 73] – among SGM persons. For Aim 1, using conservative estimates, we expect a sample size of *N* = 500 in each SGM subgroup to provide a minimum of 98% power (normal approximation with continuity correction) to detect a 15% absolute difference in depression prevalence (estimated prevalence ratio of 1.6) between exposed and unexposed persons. We also expect this sample size to provide at minimum 98% power for a 15% absolute difference in both suicidal ideation and attempts. For the LCA, estimates of minimum required sample sizes in growth mixture models with 10 exposure measures ranged from 300 to 1,100 (in a six-class model with low class separation and 20% missing data) based on Monte Carlo simulations [74]. With an estimated 13 indicators of distal minority stressors, our total sample of 2,500 should therefore be adequate for estimating growth mixture models.

All participants will be followed for 12 months with a projected overall retention rate of 80% resulting in *N* = 400 participants in each SGM subgroup available for endline analyses. We will use the same retention procedures successfully implemented in a recent online prospective pilot study with gay men and other men who have sex with men that demonstrated retention rates of 98% at four months [75]. Though retention is not expected to vary by SGM subgroup, our Aim 2 power calculations account for expected variations in terms of the prevalence and incidence of depression and suicide attempts. Drawing on one general population study of depression incidence over a 24-month period [76], we have used a conservative estimate of average annual incidence of one-eighth of the estimated prevalence. We have also extrapolated from existing cross-sectional studies [7, 34, 66, 72, 73, 77, 78] to estimate that between 25–30% of participants will have additional exposures to distal minority stressors over the follow-up period.

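### Class enumeration compares latent class models only with one another, so a single severity gradient would be reported as classes, and subgroups differing only in mean severity could show different class counts

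*Protocol article*

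**What the plan says.** The first aim, at the end of the Background, is to "determine whether classes of stigma, discrimination, and traumatic experiences vary across subgroups of rural SGM adults" and whether those classes relate to the prevalence of depression, suicidal ideation and attempts. The second aim carries the same classes forward as the exposure for incidence.

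Under Data analysis, the candidate set is fixed: "we will perform class enumeration by testing models with an increasing number of classes". The choice among candidates is then described: "The best fitting model will be selected using fit indices such as the Akaike Information Criteria, Bayesian Information Criteria", with the Vuong-Lo-Mendell-Rubin test and entropy also named. The chosen model is "further evaluated based on theoretical interpretability".

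The same section adds that "All initial analyses will be conducted separately by the five SGM subgroups". Alignment is used to examine measurement invariance, and groups are combined if their classes turn out alike.

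The Sample size section gives the dimensions of each run: "we expect a sample size of *N* = 500 in each SGM subgroup" and "With an estimated 13 indicators of distal minority stressors". Primary exposures draws these indicators from four instruments: enacted stigma, day-to-day discrimination, childhood adversity and life events.

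**The concern.** Every candidate assumes discrete classes with items independent within class. The only candidate without distinct classes is the one-class model, which requires the stressor items to be mutually unrelated. That is implausible for discrimination, violence and harassment items, several of them from one scale. If people differ mainly in how much they have been exposed, no candidate can represent that, and the fit criteria will cut the gradient into bands.

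The consequence is sharpest for the first half of Aim 1. How many bands the data support depends on where a subgroup sits on the gradient as well as on item strength. The Sample size section itself expects cisgender sexual minority men to have the lowest incidence of distal stressors. A difference in amount could therefore appear as a difference in class structure, and could also block the pooling step, which depends on the classes being alike.

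**Working it through.** The plan states no error rate for class enumeration, so there is no figure to reproduce. The check asks what the stated rule returns when the truth is known.

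**Inputs from the protocol article.** 13 indicators and N = 500 per subgroup (Sample size); AIC, BIC, a likelihood-ratio test and entropy (Data analysis).

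**Assumptions.** Binary items, a normal severity trait, mean item slope 0.5 to 2.0, item prevalence 15–60% or 5–30%.

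**Parameter counts.** A K-class model has 13K + (K − 1) parameters: 13, 27, 41 and 55 for K = 1 to 4. A one-factor (two-parameter logistic) model has 2 × 13 = 26.

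**What two classes must beat.** BIC = −2 log L + k ln N, and ln 500 = 6.21. Moving from one class to two costs (27 − 13) × 6.21 = 87.0 under BIC and 14 × 2 = 28 under AIC. As a stand-in for the Vuong-Lo-Mendell-Rubin test, the 95% point of the one-versus-two-class likelihood ratio (LR) in 60 simulated one-class data sets was 37.7.

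**Truth: one continuum, no classes.** Class count chosen by BIC among one to four, 100 data sets per row:

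| Slope | Prevalence | Alpha | 1 class | 2 classes | 3 classes | Smallest LR |
|---|---|---|---|---|---|---|
| 0.5 | 15–60% | 0.40 | 58 | 42 | 0 | 43.9 |
| 0.7 | 15–60% | 0.56 | 0 | 100 | 0 | 126.4 |
| 1.0 | 15–60% | 0.70 | 0 | 94 | 6 | 328.4 |
| 1.5 | 15–60% | 0.82 | 0 | 1 | 99 | 753.0 |
| 2.0 | 15–60% | 0.88 | 0 | 0 | 100 | 1191.2 |
| 1.0 | 5–30% | 0.63 | 0 | 100 | 0 | 157.1 |
| 1.5 | 5–30% | 0.78 | 0 | 57 | 43 | 421.5 |

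From alpha 0.56 upward, even the smallest LR exceeds 87.0. At alpha 0.40 it still exceeds 28 and 37.7, so AIC and the simulated test favour two classes over one in every row. Wherever BIC chose two or more classes, the item profiles were ordered (low/high or low/medium/high).

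**Entropy gives no warning.** Mean entropy at the BIC solution was 0.55 to 0.82 under a continuum, against 0.76 with three real non-ordered classes.

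**A larger sample does not help.** At N = 2,500 and slope 1.5, BIC chose three classes in 5 of 8 data sets and four in the other 3.

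**Only mean severity shifted.** Same continuum, slope 1.5, thresholds −1 to 2, N = 500, 30 data sets per mean, BIC:

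| Trait mean | 2 classes | 3 classes |
|---|---|---|
| −1.5 | 29 of 30 | – |
| −0.75 | 11 of 30 | 19 of 30 |
| 0 | – | 29 of 30 |

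A separate run of the same kind moved from two classes in 17 of 20 data sets to three in 20 of 20.

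**Controls.** With independent items BIC chose one class in 40 of 40 (AIC chose two or more in 18 of 40). With three real non-ordered classes BIC chose three in 30 of 30.

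**Adding a one-factor model to the BIC comparison.** It was preferred in 98–100% of continuum data sets at slope 0.7 or more, and in 56–60% at slope 0.5. It was never preferred with three non-ordered classes (0 of 30) or independent items (0 of 40). It was, however, preferred in 40 of 40 data sets with three genuine ordered classes, and in 40 of 40 with four. Against three classes it saves (41 − 26) × 6.21 = 93.2 BIC points in penalty. With four separate continuous factors it beat the class models in 40, 37 and 29 of 40 at inter-factor correlations of 0.5, 0.3 and 0.2.

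**The case against.** **This is a condensed article.** A fuller plan may name a comparator, and the list of indices is open-ended. That is fair as far as indices go. The candidate set, however, is stated, and every index named either compares class models with each other or describes class separation. Alignment addresses invariance across subgroups, not classes against a gradient.

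**The aims do not claim that classes are natural types.** A reader might infer that both aims rest on proving that classes exist. They do not: they ask about variation and association, and latent class analysis can serve as a summary of co-occurring exposures. Classes that cut a continuum can still predict outcomes, and no bias in an association has been shown. What remains is the question of variation across subgroups, which is itself a stated aim.

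**Interpretability could catch ordered profiles.** It could, since the ordering is visible in a profile plot. But no criterion says that ordered profiles would be treated differently, and low/medium/high is easy to interpret.

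**A single factor over four instruments is an assumption.** It is. With three correlated factors, though, the rule still returned two or more classes in 60 of 60 data sets, so the defect does not depend on there being one dimension.

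**A one-factor comparator cannot decide the matter.** This stands. It wins against genuine ordered classes and often against several separate dimensions, so it should not replace the exposure automatically.

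**Conclusion.** The point holds in limited form and is worth acting on. When the indicators are at least modestly correlated (alpha about 0.56 or more in these simulations), the stated rule returns two or more classes under a pure severity continuum, and subgroups that differ only in mean severity can return different counts. At risk are the conclusion that classes vary across subgroups and the pooling decision.

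Two stronger readings are not supported. One is that the rule finds classes whatever the truth: independent items gave one class by BIC in 40 of 40, and at alpha about 0.40 BIC chose two or more in only 42 of 100. The other is that class-outcome associations are invalid: bands of a gradient can carry a real dose-response, and the issue is how they are described.

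The sizes rest on assumed slopes, thresholds, prevalences and mean shifts. The article gives no item correlations or severity gaps and has not yet selected its indicators. The likelihood-ratio test was judged against a simulated null, not computed in its published form.

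**What to change.** In Data analysis, add for each of the five subgroups two dimensional comparators on the same indicators: a one-factor model and a correlated-factor model with factors defined by instrument. Report their BIC beside that of the selected class model, together with the class profiles.

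Keep the classes as the planned exposure. State in advance that, if a dimensional model fits better or the profiles are purely ordered:

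- the classes will be described as severity bands, not distinct exposure patterns;
- differing class counts will not be read as differing types across subgroups;
- the Aim 1 and Aim 2 associations will also be reported with the continuous severity score or scores, as a sensitivity analysis.

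Do not make BIC an automatic switch of the primary exposure.

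The cost is 2 × 5 = 10 extra models plus the sensitivity associations, on data already being collected, and possibly a more modest interpretation of the classes.
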